#### 2.6.2. Secondary Outcomes

##### Switch Activation

Switch activation is defined as when the switch is pressed to activate the modified ride-on car and make it “go”, thereby moving in space from one place to another [30]. Switch activation may occur from the child in the modified ride-on car independently or with assistance (either physical or verbal cueing) from others. Assistance may be provided by a sibling or peer, or an adult such as a parent/caregiver or clinician. The duration of switch activation, who activated the switch, and the level of assistance, if any, provided to the child using the modified ride-on car will be coded. Total switch activation time (minutes and seconds) and percentage of time of each 10-min video will be coded and reported. Switch activation analyses will be carried out at the end of week 4, 8, and 12 of the intervention.

Inter- and intra-rater reliability (at least 85% agreement) will be established on 10% of the video recordings amongst one expert coder and two secondary coders. Training will include coding of video recordings, discussion of disagreements, and coding of additional videos until reliability is established. All videos will be coded in Datavyu.

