### 2.7. Intervention

Modified ride-on car training sessions will be conducted three times a week at the participants’ home or in the clinic, according to family preference. A therapist will guide the sessions at both locations. The intervention session will include the following: (1) environment setup (e.g., instructing families) (5 min); (2) natural play as a warm up activity (5 min); and (3) social training and mobility with modified ride-on cars (30 min). The focus of treatment sessions will be based on the social function goals and the expected mobility set by caregivers in the modified GAS after the pretest [36]. The 30-minute driving session will involve the participants learning cause–effect concepts by driving the modified ride-on car (i.e., pressing the switch for moving and releasing it for stopping). The dose of the intervention will be adjusted considering the opinion of the parents who participated in a previous interview and the results of a recent study, where the average time of interventions was 24 to 30 min [37]. The therapist and caregivers then will use verbal and physical cueing to encourage children to drive and explore the surrounding environment [17,38]. All sessions will be video- and audio-recorded. Figure 2 shows a modified ride-on car and a child with CZS.

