### 2.8. Modified Ride-On Cars

Ride-on cars will be modified with a joystick for activation. Joystick control will allow omni-directional turning and proportional speed-control. The vast majority of research with modified ride-on cars has installed a large, easy-to-press, all-or-nothing activation switch that does not provide turning nor speed control. These steering and speed modifications will enhance the ability for young children with CZS to explore the environment and use the device within the home and community. Joystick activation ensures that children are provided with an opportunity to use an activation method that is consistent with future joystick-driven device options, such as motorized wheelchairs. Ride-on cars will be modified with optimal seating support using readily available, low-cost materials based on each child’s individual needs. Ride-on car models will be selected based on their design and structure to provide seating support. 

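### The switch-activation outcome is worded for a press switch while Section 2.8 describes a joystick, and the summary named for it mixes the child's own driving time with assisted time

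*Protocol article*

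**What the plan says.** Section 2.6.2, Switch Activation, gives the definition: "Switch activation is defined as when the switch is pressed to activate the modified ride-on car". It then says whose activation counts: "Switch activation may occur from the child in the modified ride-on car independently or with assistance (either physical or verbal cueing) from others". Among the items recorded, besides duration, it lists "who activated the switch, and the level of assistance, if any, provided to the child using the modified ride-on car will be coded". For the summary it states: "Total switch activation time (minutes and seconds) and percentage of time of each 10-min video will be coded and reported". Measurement is at the end of weeks 4, 8 and 12.

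Section 2.7 describes what the child learns in the 30-minute driving part of each session as "pressing the switch for moving and releasing it for stopping", with the therapist and caregivers prompting the child by voice and by hand.

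Section 2.8 describes the control differently: "Ride-on cars will be modified with a joystick for activation". It continues: "Joystick control will allow omni-directional turning and proportional speed-control". It sets this against most earlier research, which it says used a "large, easy-to-press, all-or-nothing activation switch that does not provide turning nor speed control".

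Section 2.9 assigns the Friedman test to numerical data with more than two measurements. That covers switch activation, which has three.

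**The concern.** Two things looked wrong.

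First, the outcome and the training task are worded for the type of control that Section 2.8 says this trial departs from. A duration needs a start and a stop. A press switch supplies both without further rules. A proportional joystick is moved by degrees, so the coder needs to know whether a slight deflection, a slow creep or a turn on the spot counts. The 85% agreement requirement does not settle this, because coders can agree on an arbitrary rule.

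Second, help is part of the intervention and can differ between children and between weeks. If assisted time counts towards the only summary named, a rise may mean that adults helped more, and a flat line may hide a child who now drives with less help. The study has one group, so no comparison arm would separate the two. Its stated purpose includes informing a larger randomized trial, and an ambiguous driving measure could be carried into it.

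**Working it through.** No figure in the protocol depends on this point, so there is none to reproduce. The check is a comparison of sections, followed by a short piece of arithmetic on the named summary.

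**1. The control**

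| Section | Subject | Control described |
|---|---|---|
| 2.6.2 | Outcome definition | Switch, pressed |
| 2.7 | Driving task | Switch, pressed and released |
| 2.8 | Device | Joystick, with steering and graded speed |

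Sections 2.6.2 and 2.7 agree with each other, and neither agrees with Section 2.8. Section 2.8 does not use switch and joystick as two names for one thing: it presents the joystick as the departure from the switch. The three sections cannot all describe the same car as they are worded.

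**2. The summary**

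For one clip of 10 min, let I be the time the child activates the car alone, A the assisted time, and T the total. By the definition in Section 2.6.2:

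- T = I + A
- reported percentage = 100 × T / 10
- change in T = change in I + change in A

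The change in T equals the change in I only if A stays constant, and nothing in the plan holds help constant. For a given T, I can lie anywhere from 0 to T. If T = 3.0 min, the reported value is 30%, and independent driving may be anything from 0% to 30% of the clip.

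**3. Illustration**

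The minutes below are assumptions, since the protocol gives no activation times.

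| | Total T | Assisted A | Independent I = T − A | Reported 100 × T/10 |
|---|---|---|---|---|
| Week 4 | 3.0 | 2.0 | 1.0 | 30% |
| Week 12 | 3.0 | 0.5 | 2.5 | 30% |

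The reported outcome does not move, while independent time rises by (2.5 − 1.0)/1.0 = 150%. With the two weeks exchanged, the reported outcome is again 30% both times, while independent time falls by (2.5 − 1.0)/2.5 = 60%. The total alone cannot tell these cases apart. The coded items can, since A and I are recoverable from who activated and the level of help.

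**The case against.** The case on the other side is substantial.

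- **The definition is partly functional.** Section 2.6.2 ties activation to making the car go and move through space, and Section 2.8 calls the joystick a means of activation. Time in which the control moves the car can be coded from video for either control. This stands. A reader might infer that the outcome has no valid definition, but the text does not support that.
- **Start/stop learning is what Section 2.7 trains.** A reader might infer that the outcome fails to measure the driving this trial trains. Section 2.7 says the sessions teach starting and stopping, with prompting, and activation time captures that. This stands too. What activation time leaves out is steering and graded speed, the features Section 2.8 adds.
- **The split is already coded.** Who activated and the level of help are recorded, and the article does not say that only the total will be reported. This stands as a limit on the harm: the information is not lost. The article nevertheless singles out the total and its percentage, and that is the summary that moves with help.
- **Detail belongs elsewhere.** Fine coding rules and the choice of test variable are often left to a coding manual or analysis plan, which are not shown. Their absence alone would be no finding. The contradiction on the control, however, is between statements in the article itself.
- **Learning is measured by another tool.** The ALP rates driving performance in phases 1 to 8 at weeks 4, 8, 12 and follow-up. This stands and lowers the weight of the point.
- **Total time is a reasonable measure of use** for children at GMFCS level IV or V. It is, which is why it should be kept beside the split.

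**Conclusion.** The point holds in a limited form. The article contradicts itself on the control fitted to the cars, and the outcome definition follows the version that Section 2.8 does not describe. Separately, the only summary named for reporting combines independent with assisted activation, so its course over weeks 4, 8 and 12 cannot be read as the child's own progress.

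The size is moderate to minor. Switch activation is one of several secondary outcomes in a feasibility study of 10 children whose primary outcome is feasibility. No sample size and no primary conclusion rests on it. The minutes in the illustration are invented and show only that a total can hide a split, not how often it would. The second part assumes that the amount of help varies between time points, which is plausible because prompting is part of the sessions, but the protocol gives no data on it. Nothing here decides which control is the right one.

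**What to change.** 1. Reconcile Sections 2.6.2, 2.7 and 2.8 on which control is fitted, and use one term for it throughout.
2. State the onset and offset of activation for that control. If it is a joystick, a workable rule is onset at a displacement from neutral that moves the car, and offset at the return to neutral.
3. Report independent child-initiated time and assisted time separately, beside the total.
4. Name independent time, as a percentage of the clip, as the variable that enters the Friedman test over weeks 4, 8 and 12.

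The cost is a change of wording and a revised coding sheet before coding starts. No new data are needed, because who activated and the level of help are already to be coded. The downside is a less direct comparison with earlier press-switch studies; keeping the total in the report retains part of it.

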##### Daily Driving Journal

Parents will record the date, duration (minutes) location, and activities during each driving session in a daily driving journal. The researcher will collect the daily driving journal at the end of the study. The daily driving journal for entries of week 4, 8, and 12 of the intervention, and in the follow-up will be analyzed.

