Several studies have showed the results of a powered mobility intervention with modified ride-on car on the behavior and development of young children with disabilities, including CP. Although none of the children in these studies were formally referred to use powered mobility devices due to their young age or diagnosis, all demonstrated the ability to independently press the activation switch, enjoyed driving sessions, and some experienced increased self-care mobility [16], social skills [16,17], as well as increased peer interaction on the playground [18], and during an inclusive playgroup [19]. The limitations of previous work includes a heavy reliance on low-evidence level research designs (i.e., case reports and case series); the inclusion of participants with varying disabilities in the same sample; and the reporting of a wide variety and often very low adherence rates to recommended use guidelines. These limitations have hindered the interpretation and generalization of study results and will be addressed in the current protocol. 

Although participation-based interventions are a promising strategy not only to improve participation but also body functions [20], there are no evidenced-based practices to guide clinical recommendations of early powered mobility device use, including modified ride-on cars, for young children with disabilities, including CZS. The current protocol will address this gap in knowledge and will have a direct and immediate impact on clinical practice. From a global health standpoint, the results may provide an evidence-based rehabilitation option that will be relevant to early child development in low resource contexts. The objective of this study is to determine the feasibility of a powered mobility intervention for young children with CZS with severe motor impairment including acceptability and effectiveness. The specific aims are:To evaluate the acceptability of a modified ride-on car intervention for young children with CZS and their families.To determine the effect of a modified ride-on car intervention on the (a) mobility and social function, and (b) participation of young children with CZS and their families.To understand the barriers and facilitators of a modified ride-on car intervention for young children with CZS and their families.

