## 2. Materials and Methods

### 2.1. Design

This is a feasibility trial of a mixed-methods case series, prospectively registered, with 3-month intervention and 1-month follow-up. The follow-up will aim to assess preliminary learning retention and implications of modified ride-on car training sessions [16]. This prospective study will provide important information about the feasibility, assistive effectiveness, and rehabilitative effectiveness of the first intervention focusing on powered mobility for children with CZS in Brazil. The procedures and timeline of the study are included in Figure 1 and Table 1.

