### 2.6. Outcomes Measures

#### 2.6.1. Primary Outcome

The primary outcome of the study will be the feasibility of the protocol, including a narrative description, recruitment and retention rates, adherence and acceptability of the protocol. A mixed methods approach will be used to assess the primary outcome.

A document analysis will determine the number of parents who received information about the study by mail, the number of potential participants contacted by telephone, how many parents met the inclusion criteria and how many provided informed consent, received, and completed the intervention. 

Qualitative data will be collected using the photovoice method and focus groups. Photovoice is a participatory action-research modality that uses photographs to express individuals’ experiences during their daily realities [23].

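### Parents log every driving session, but only weeks 4, 8, 12 and follow-up are analysed, so 9 of 12 intervention weeks of journal data go unused

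*Protocol article*

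**What the plan says.** Under Secondary Outcomes (section 2.6.2), the Daily Driving Journal paragraph sets three rules.

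- Recording covers every drive: "Parents will record the date, duration (minutes) location, and activities during each driving session in a daily driving journal".
- Collection happens once: "The researcher will collect the daily driving journal at the end of the study".
- Analysis is restricted: "The daily driving journal for entries of week 4, 8, and 12 of the intervention, and in the follow-up will be analyzed".

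Table 1 marks the journal at weeks 4, 8, 12 and 16, the same points as the parent feasibility questionnaire (PFQ) and the assessment of learning powered mobility (ALP). Switch activation shares the first three. Section 2.1 describes a study "with 3-month intervention and 1-month follow-up", and Table 1 places training in weeks 1–12 only. Section 2.7 states: "Modified ride-on car training sessions will be conducted three times a week at the participants’ home or in the clinic". It adds that a therapist guides the sessions at both locations and that all sessions are recorded on video and audio.

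Section 2.6.1 defines feasibility, the primary outcome, as "including a narrative description, recruitment and retention rates, adherence and acceptability of the protocol". Section 2.9 separately compares scheduled with completed treatment sessions and names no particular weeks.

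**The concern.** The families do the work of logging each drive for the whole study, and the plan then uses a quarter of the intervention weeks. The article gives no reason for the restriction.

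This matters because the protocol presents actual use of the car as something earlier studies handled poorly. Among the limitations it says it will address, the Introduction lists "the reporting of a wide variety and often very low adherence rates to recommended use guidelines". One of its aims is to understand barriers and facilitators, for which the first weeks are informative. None of weeks 1 to 3 is analysed. The three analysed weeks are also those in which the family is assessed, so they are not a neutral sample of ordinary weeks.

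**Working it through.** The protocol states no figure for the share of journal data used, so there is none to reproduce. The check is a direct count, then a test of whether the restriction has a predictable direction of error.

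**Inputs.** Intervention length: 12 weeks (Table 1). Analysed intervention weeks: 4, 8 and 12 (Daily Driving Journal). Guided sessions: 3 per week (section 2.7). Children: 10 (section 2.3).

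**Share unused.** 1 − 3/12 = 9/12 = 75% of intervention weeks. In planned guided sessions, 12 × 3 = 36 per child would be logged and 3 × 3 = 9 analysed, leaving 27 unused. Over weeks 1–16 the unused share is 12/16 = 75% if follow-up means week 16 alone, or 9/16 = 56% if it means weeks 13–16.

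**Does the journal cover anything the session records do not?** Three places suggest that it does:

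- The PFQ (section 2.6.1) asks about time of use at home and in the community, whereas guided training takes place at home or in the clinic.
- The photovoice script asks when and where the car is used.
- The journal is analysed at follow-up, after guided training has ended in Table 1.

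Use outside guided sessions is therefore expected. Session recordings and the scheduled-versus-completed count cannot show it. The PFQ asks about time of use, but only at weeks 4, 8, 12 and follow-up, so it does not fill the gap.

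**Direction of error.** The patterns below are assumptions, not figures from the documents. Use is expressed as a percentage of some nominal weekly amount.

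| Assumed pattern over weeks 1–12 | Mean, weeks 4, 8, 12 | Mean, all 12 weeks | Difference (points) |
|---|---|---|---|
| Flat at 70% | 70.0 | 70.0 | 0 |
| Linear fall, 90% to 40% | 58.2 | 65.0 | −6.8 |
| Linear rise, 40% to 90% | 71.8 | 65.0 | +6.8 |
| 80% in assessment weeks, 60% otherwise | 80.0 | 65.0 | +15.0 |
| 50% in assessment weeks, 70% otherwise | 50.0 | 65.0 | −15.0 |

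Example for the fourth row: (3 × 80 + 9 × 60)/12 = 780/12 = 65. The linear patterns give an error because the analysed weeks average (4 + 8 + 12)/3 = week 8, while the period averages (1 + 12)/2 = week 6.5. Three weeks cannot tell these patterns apart, so the data as analysed would not show which error had occurred.

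**The case against.** The strongest reply is that adherence does not rest on the journal. Adherence belongs to the primary outcome, but the article never says it is derived from the journal, which is a secondary outcome. Section 2.9 has its own unrestricted comparison of scheduled and completed sessions. Guided sessions are therapist-led and all recorded, so the journal is not the only source for their duration or content. This stands, and it limits the point to use outside guided sessions.

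A reader might go further and infer that adherence will be overstated. For example, a family driving three times in each analysed week and once in each of the other nine would average (9 + 9)/12 = 1.5 sessions per week, while the analysed weeks show 3.0. The documents do not support that inference. The pattern is invented, and other patterns push the error the opposite way. If these were guided sessions, the section 2.9 comparison would show 18 of 36 completed, or 50%.

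A reader might also infer that journals from families who withdraw are lost. The article does not say so, and handling of withdrawals is commonly left to the full protocol. What can be said is that a single collection at the end allows no check of entries along the way.

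Two further defences have some force. Aligning the journal with the other instruments suits the Friedman test planned for more than two measurements, but the remaining entries can be analysed without giving that up. The sentence could also mean all entries accumulated up to each time point, in which case nothing is unused. The wording favours single weeks, and if the cumulative meaning was intended the sentence needs correcting anyway.

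**Conclusion.** The point holds in a limited form. On the plain reading, 75% of intervention weeks of journal data already recorded are not analysed. The total amount, location and weekly course of use outside guided sessions cannot be recovered from the three weeks kept, and the start-up weeks are missing entirely. The error may go either way, and its size depends on a pattern of use that the documents do not give.

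The conclusion rests on two assumptions: that the named weeks mean single weeks, and that some driving happens outside guided sessions, which the protocol implies without stating it. Session adherence as measured in section 2.9 is unaffected. This is a worthwhile improvement to a secondary outcome that informs feasibility, and not a threat to the primary outcome.

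**What to change.** Replace the analysis sentence in the Daily Driving Journal paragraph with wording such as:

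*All journal entries from week 1 to the end of follow-up will be analysed (sessions and minutes per week, location and activities, per child), with the week 4, 8, 12 and follow-up values kept for the repeated-measures comparison.*

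Also state that the journal is copied or photographed at the existing week 4, 8, 12 and 16 assessments, so that gaps can be seen while the study is running.

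No new instrument or visit is needed. The cost is data entry: for guided sessions, about 36 × 10 = 360 entries in the intervention period instead of 9 × 10 = 90, plus whatever the 10 families log outside those sessions.

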##### Pediatric Evaluation of Disability Inventory–Computer Adaptive-test (PEDI-CAT)

The PEDI-CAT is the computerized version of PEDI and has been translated and adapted culturally to Brazil [33]. It is answered by the children’s caregiver and has an item bank divided into two domains: (1) mobility, which includes 75 items ranging from basic motor skills (e.g., sitting without support) to more difficult motor skills (e.g., running or climbing a step ladder). Additionally, this domain includes the use of walking devices; (2) cognitive/social, which includes 60 items related to interaction (e.g., follows the gaze of another person), communication (e.g., uses gestures to ask for something), everyday cognition (e.g., recognizes his/her name), and self-management (e.g., when upset response without hitting). In these domains, the four-point scores (unable, hard, a little hard, easy) are based on different levels of difficulty. The overall score is transformed in a normative score (based on age) and a continuous score that will be used in the analyses. The PEDI-CAT will be administered on the baseline and at the end of the 12th week of the intervention.

